#### 7.1.1 Clinical Care

For the neurosurgical group patient management will take place according to usual care. When patients meet the inclusion criteria, an ALA-patch will be placed in the preoperative phase and 3 hours later. After at least 4 hours of PpIX induction, the cutaneous mitoPO2 sensor will be placed to make the first measurements after which measurements of the mitoPO2 will be made at predefined moments.

## 7.2 Data collection

While waiting for the induction of PpIX after placement of the ALA patch, baseline data will be gathered. Appendix 2 shows an overview of the data collection. First of all, demographic data will be collected: age in years, sex, weight, height, Body Mass Index, allergies, medication use, comorbidities (acute and chronic), and type of surgery. Also, APACHE (Acute Physiology and Chronic Health Evaluation)-II and APACHE-IV will be assessed. The demographic data can be obtained from the hospital's electronic patient dossier system (EPD). Information regarding perioperative characteristics will be collected as well, including the length of operation, type of anaesthetics used and perioperative complications.

Clinical data will be assessed pre- as well as intra- and postoperatively including heart frequency (HF), blood pressure (BP), and peripheral measured oxygen saturation (SpO2). Postoperatively, these will be assessed at the same time points as the mitoPO2 measurements. Other data, if applicable, collected from the EPD are: vasopressor use, inotropic therapy, mechanical ventilation duration and settings, PaO2/fractional inspired oxygen (FiO2) ratio, and Alveolar-arterial gradient. Interventions given to patients in the ICU or MC, such as intravenous fluid therapy, transfusion, medication and/or procedures, will be noted. No extra samples will be taken from patients. Appendix 2, figure 2 gives an overview of measurements part of standard care, and which of those measurements are part of the study.

At certain time points, described in detail in the next section, mitoPO2 measurements will be done. Signal quality will be measured using the COMET monitor device itself, where a higher signal quality corresponds with a stronger PpIX signal and a more sensitive mitoPO2 measurement. In a previous study it was shown that for PpIX-based delayed fluorescence measurements a signal-to-noise ratio > 20 limits the noise-induced potential error in mitoPO2 measurements below 2% over the physiological PO2 range. Signal-to-noise ratio (SNR) in time domain lifetime measurements (as implemented in the COMET) is commonly defined as the ratio of maximal signal amplitude (at the start of the decay) to the maximum signal of the noise (peak-to-peak). Since SNR was not regarded to be an intuitive measure for the end user of a COMET device, the software converts SNR to signal quality using a non-linear relationship in which e.g. a SNR of 100 provides a signal quality of almost 80%. In a previous study, it was shown that for PpIX-based delayed fluorescence measurements, a signal-to-noise ratio > 20 limits the noise-induced potential error in mitoPO2 measurements below 2% over the physiological PO2 range. A signal quality of 25% corresponds to a SNR of 20, can easily be obtained in practice and keeps the noise-induced uncertainty in the measurement to an acceptable low level of less than 2%. This is why we choose to (arbitrarily) define 25% as the minimum required signal quality for a feasible measurement. Between-subject variability is defined as the variation of mitoPO2 at each measurement time point in the study population. Therefore, mean mitoPO2 and standard deviation (SD) is calculated per measurement time point. This SD represents the between-subject variability. Within-subject variability is defined as the variation of mitoPO2 within one subject at each measurement time point, since multiple measurements are taken at each timepoint. Since a mean mitoPO2 at each timepoint is used, the

standard deviation of this measurement per participant is calculated. The mean of this SD represents the within-subject variability of the study population.

All data will be entered after validation in a study database for subsequent tabulation and statistical analysis. The data will be handled confidentially and anonymously. Patients re-admitted to the ICU or MC and already participating in this study will only be followed according to the study protocol. Thus re-admitted patients will not be included in the study for the second time.

*Figure 4: MitoPO2 measurement with the COMET*

### 7.2.1 Sample handling and Measurements:

In order to further investigate the between- and within-subject variability of mitoPO2 over time, mitoPO2 measurements will be performed over a 24-27 hour period per patch.

For the first patch these moments are:

- 4 hours after ALA-induction (Directly after surgery in patient group) (=T0)
- 1 hour after T0 (=T1)
- 3 hours after T0 (=T2)
- 6 hours after T0 (=T3)
- 24 hours after T0 (=T5)
- 27 hours after T0 (=T6)

[figure not shown]

Patch 2 is applied 3 hours after the first patch, with measurement moments corresponding to patch 1 with overlap (see table 2):

- 4 hours after ALA-induction (=T0)
- 1 hour after T0 (=T1)
- 3 hours after T0 (=T2)
- 21 hours after T0 (=T4)
- 24 hours after T0 (=T5)

Table 2: Overview of measurement moments for each patch (shading indicates overlapping moments).

| Patch # | Measurement | Hours after 4 hours ALA-induction | Comments                                    |
|---------|-------------|-----------------------------------|---------------------------------------------|
| 1       | T0          | 0                                 | Directly postoperatively (in patient group) |
| 1       | T1          | 1                                 |                                             |
| 1       | T2          | 3                                 |                                             |
| 2       | T0          | 0                                 | 3 hour offset relative to patch 1           |
| 2       | T1          | 1                                 |                                             |
| 2       | T2          | 3                                 |                                             |
| 1       | T3          | 6                                 |                                             |

|   |    |    |  |
|---|----|----|--|
| 1 | T5 | 24 |  |
| 2 | T4 | 21 |  |
| 1 | T6 | 27 |  |
| 2 | T5 | 24 |  |

### 7.3 Withdrawal of individual subjects

Subjects can leave the study at any time for any reason if they wish to do so without any consequences. The investigator can decide to withdraw a subject from the study for urgent medical reasons. These subjects will not be subjected to follow-up.

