## 5.2 Use of co-intervention

Due to the risk of phototoxicity, it is important for the skin exposed to the ALA patch to be protected from sunlight during, between, and for 24 hours following measurements.

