### 8.3 Adverse events (AEs)

Adverse events are defined as any undesirable experience occurring to a subject during the study, whether or not considered related to the investigational product. All adverse events reported spontaneously by the subject or observed by the investigator or his staff will be recorded.

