## 8.7 Follow-up of adverse events

All AEs will be followed until they have abated, or until a stable situation has been reached. Depending on the event, follow up may require additional tests or medical procedures as indicated,

and/or referral to the general physician or a medical specialist. SAEs need to be reported until end of study within the Netherlands, as defined in the protocol

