### **10.3 Objection by minors or incapacitated subjects**

Section 4, subsection 2, of the WMO stipulates that a legally incompetent adult cannot be forced to undergo a treatment or behave in a particular manner in the context of non-therapeutic research against his or her will. Subjects younger than 18 years are already excluded from the study. We don't expect patients that are not capable for the informed consent procedure. If there are adults, that are incapable of giving informed consent, a legal representative will be asked to give informed consent according to the GCP guideline. When the subject is able to give informed consent after being included in the study by consent of the legal representative and denies any further participation, the subject will be excluded from the study without any consequences. The data collected up to that point will be used for analysis. No additional data will be collected.

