*d. Selectivity of the mechanism to target tissue in animals and/or human beings*

Not applicable.

*e. Analysis of potential effect*

The PpIX-TSLT technique as well as the COMET have been investigated and have been proven safe, as demonstrated by studies on volunteers and patients. The possible effect of phototoxicity after PpIX induction is a potential risk, but the PpIX-TSLT uses short-pulsed excitation and a fraction of the total light dosage used in photodynamic therapy. This risk is therefore considered to be very low. We expect no effects of the measurement for the patients (aside from reported temporary mild discomfort like erythema and pruritus associated with the topical application of ALA). During the pilot study of the INOX ICU-2 study, no side effects besides mild pruritis in 1 patient was seen, confirming the expected low risk.

*f. Pharmacokinetic considerations*

Not applicable.

*g. Study population*

Postoperative patients in the ICU are vulnerable patients. According to GCP guidelines, a non-therapeutical study can only take place if it has a likelihood of benefit for group represented by the subject. With the results of this study potential factors affecting the variance of the mitoPO2 measurements could be better understood, and applied, ranging from postsurgical to critical ill patients to reduce measurement error, and therefore assist us in the interpretation of the mitoPO2 measurements. The effect of time-since-application of the ALA-patch will also be studied in a cohort of healthy volunteers. This study entails low risk and burden for the subjects since it is a non-invasive measurement with no known serious adverse reactions.

*h. Interaction with other products*

None expected, see Alacare product information.

*i. Predictability of effect*

No effect of the measurements is expected. Minor temporary skin lesions can occur, as seen in the healthy volunteers. With the COMET we expect less effect, due to progressive technique since the study in healthy volunteers, so the light intensity and total light dosage will be even less.

*j. Can effects be managed?*

No effects of the mitoPO2 measurements are expected, but when there is any indication of a skin lesion (e.g. unexpected pain during the measurements), the measurements can and will be stopped.

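### Section 7.3 ends follow-up for withdrawn subjects, including those withdrawn on medical grounds, while Section 8.7 requires every adverse event to be followed to resolution or stability

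*Protocol*

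**What the plan says.** Section 7.3 (Withdrawal of individual subjects) describes two routes out of the study. Subjects may leave at any time for any reason. In addition: "The investigator can decide to withdraw a subject from the study for urgent medical reasons". The section then closes with: "These subjects will not be subjected to follow-up". It does not say which kind of follow-up is meant, and it makes no exception for an event that is still open.

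Section 8.7 (Follow-up of adverse events) states: "All AEs will be followed until they have abated, or until a stable situation has been reached". It allows for further tests, procedures or referral as needed. It makes no exception for subjects who have left or been withdrawn.

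Section 10.3 holds the only explicit limit on data collection after a subject stops. It concerns a subject entered through a legal representative who later regains capacity and refuses to continue. Data gathered up to then are kept, and "No additional data will be collected".

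Adverse events are a stated objective (Section 2.2) and a secondary outcome (Section 9.2).

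**The concern.** A withdrawal rule can stop two different things: study measurements and safety follow-up. Stopping measurements is harmless and often necessary. Stopping safety follow-up is not, and least of all for a subject whom the investigator has taken out on medical grounds. Section 7.3 uses one unqualified word for both, and it places the sentence directly after the one on urgent medical withdrawal.

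Two things are at stake. The first is the subject: staff who apply 7.3 as written could close the file on an unresolved event. The second is the adverse event report: an event in a withdrawn subject would appear without an outcome, or with its course cut off at the withdrawal date. Subjects withdrawn medically are more likely than others to have such an event, so the loss would not fall at random.

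**Working it through.** No calculation decides this point. It rests on setting the rules side by side and asking what each requires for the same subject.

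| Situation | Section 7.3 | Section 8.7 | Section 10.3 | Consistent? |
|---|---|---|---|---|
| Leaves by choice, no open event | No follow-up | Nothing to follow | Not applicable | Yes |
| Leaves by choice, open event, does not object to contact | No follow-up | Follow until resolved or stable | Not applicable | No |
| Withdrawn by the investigator on medical grounds, open event | No follow-up | Follow until resolved or stable | Not applicable | No |
| Entered by a representative, later refuses, open event | No follow-up | Follow until resolved or stable | No further data | 7.3 and 10.3 agree; 8.7 makes no exception |

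**Step 1: who is covered by 7.3.** The closing sentence can be taken to refer to both routes out, or only to the route named just before it. Medical withdrawals are covered on either reading.

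**Step 2: what 8.7 covers.** It applies to all adverse events. An event that began before withdrawal is an adverse event under the definition in Section 8.3, and nothing in 8.7 releases staff from following it once the subject has stopped. The conflict is therefore firm for events already open at withdrawal. It is less clear for events that begin afterwards, since 8.3 speaks of events during the study.

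**Step 3: whether another section resolves it.** Section 10.3 gives a reason to stop collecting data, namely the subject's own refusal, but only for represented subjects. It gives no ground for ending follow-up after a medical decision by the investigator. No section states which of 7.3 and 8.7 prevails.

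**Step 4: how many subjects could be affected.** Section 4.4 allows for 10% dropout: 15 × 1.1 = 16.5, taken as 17 per group. The margin is 17 − 15 = 2 per group, or 2 × 2 = 4 of the 34 subjects. If that planning allowance is taken as a rough guide to withdrawals for any reason, the conflict bites only on those among about 4 subjects who have an open event. The protocol gives no figure for that share, so the plausible range is 0 to about 4.

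**The case against.** The strongest defence is that follow-up in 7.3 means further study readings. The section sits in Methods, directly after the measurement schedule in 7.2.1, and Section 7.2 uses similar language for re-admitted patients who continue under the protocol. Adverse event follow-up has its own section, and a specific safety rule would sensibly govern a general sentence on withdrawal. Neurosurgical patients also remain under usual care (Section 7.1.1, Clinical Care) whatever 7.3 says. This reading is plausible and may well be what was intended. It lowers the weight of the point but does not remove it, because the text does not say it and a literal reader would reach the opposite result.

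Two stronger readings are tempting.

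*That a skin reaction leads straight to loss of follow-up.* Section 12, item j, says that at any sign of a skin lesion "the measurements can and will be stopped". It does not say that the subject is then withdrawn. A subject whose readings stop may simply remain in the study under 8.7, so the link to 7.3 is conditional.

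*That adverse event capture as a whole is inadequate.* Section 8.3 says: "All adverse events reported spontaneously by the subject or observed by the investigator or his staff will be recorded". The last reading on each patch falls 31 h after the first patch (4 + 27 = 31 for patch 1; 3 + 4 + 24 = 31 for patch 2), light protection continues for a further 24 h, and the text schedules no later contact. A reader might infer that late reactions in volunteers will be missed. The documents do not support that as an error. Spontaneous and observed capture is ordinary practice for a descriptive report. A later contact or reporting instruction could stand in the figures not shown or in the removed consent pages. The hyperpigmentation in 2 of 30 earlier volunteers is described only as coming after the measurements, so its onset relative to a 31 h reading is unknown. A scheduled call would be an added procedure resting on preference.

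**Conclusion.** The conflict between 7.3 and 8.7 is real and minor. As written, the two sections give opposite instructions for a subject withdrawn with an ongoing adverse event, most clearly after a medical withdrawal. If 7.3 is followed literally, safety follow-up ends for that subject and the adverse event outcome can be incomplete.

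The size is small. It concerns withdrawn subjects with an open event, probably none or very few of 34, and the local reactions that the protocol describes from earlier mitoPO2 studies were temporary. The between- and within-subject variability endpoint and the sample size do not depend on it. The conclusion assumes only that 7.3 means what it says; if the authors meant readings alone, the same edit states that meaning.

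**What to change.** Replace the last sentence of Section 7.3 with:

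> No further mitoPO2 readings are taken, but adverse events are still followed as in 8.7, unless the subject refuses further data collection (as in 10.3).

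This keeps 8.7 intact, respects a subject's refusal, and extends the principle of 10.3 from represented subjects to anyone who declines further data collection. The change is one sentence. It adds no visits, readings or calls and delays neither cohort. The only work it creates is following an open event in a withdrawn subject, which 8.7 already requires.

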## 8. Safety reporting

### 8.1 Section 10 WMO event

In accordance to section 10, subsection 4, of the WMO, the coordinating investigator will suspend the study if there is sufficient ground that continuation of the study will jeopardise subject health or safety more than was foreseen in the research proposal. The coordinating investigator will notify the accredited METC without undue delay of a temporary halt including the reason for such an action. The study will be suspended pending a further positive decision by the accredited METC. The investigator will take care that all subjects are kept informed.

### 8.2 Possible (serious) adverse events and suspected unexpected serious adverse reactions

The ALA patches are already used in and approved for the therapy of benign skin disorders with photodynamic therapy. Its use is safe and provides good treatment results with excellent cosmetic outcome. The 2x2cm large Alacare patches (8mg) were developed by Photonamic and are marketed for the treatment of actinic keratosis, a benign skin disorder, with photodynamic therapy. In dermatology, its use has been investigated. In phototherapy, the treatment effect depends on the production of singlet oxygen by photoactivation of PpIX. Excitation of PpIX induces apoptosis in cells as a result of oxygen-radical formation. In general, this requires illumination with continuous light and a high cumulative light dose (10 J/cm^2). In contrast, PpIX-TSLT uses short-pulsed excitation and a total light dosage, i.e., orders of magnitude less than used for photodynamic therapy (1 mJ/cm^2). A recent systematic review showed no significant (serious) adverse effects of ALA patches.

Side effects of ALA described with photodynamic therapy are burning of the skin (<50%, resolved in 1-4 days), burning sensation of the skin (<92%), pruritus, hyperpigmentation (22-36%), edematous lesion (35%), application site erythema (92-99%), local pain (1-92%, <30% severe), application site irritation (72%), local haemorrhage(1-4%), and headache (<10%). Most of these reactions resolved within 2 weeks. There are no reported (serious) adverse events. Since the light load at the cutaneous-PpIX-TSLT is much lower than in phototherapy, no adverse events are expected. While PpIX-TSLT is likely to be safe, the effects of phototoxicity after PpIX induction should always be considered a potential risk requiring a risk and safety assessment in any intended application.

### 8.3 Adverse events (AEs)

Adverse events are defined as any undesirable experience occurring to a subject during the study, whether or not considered related to the investigational product. All adverse events reported spontaneously by the subject or observed by the investigator or his staff will be recorded.

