### 2.2 Endpoint

In this descriptive study we aim to investigate mitoPO2's variability over the 24 hour period after ALA-induction

Specific objectives:

1. To describe the between- and within-subject variability (assessed by standard deviation) of mitoPO2 measurements over a period of 24 hours after ALA-induction.
  - a. Initially in healthy volunteers
  - b. Followed by neurosurgical patients admitted postoperatively to the ICU or MC.
2. To describe the between- and within-subject variability between 3 hour offset ALA-patches.
3. Description of between- and within-subject variability in healthy volunteers and neurosurgical patients in relation to the between- and within-subject variability of the INOX ICU-2 pilot study (P16.303).
4. Report on adverse and serious adverse events of the mitoPO2 measurements.

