### 8.8 Data Safety Monitoring Board

This is a moderate risk study in which the side effect of ALA are well described. The side effects are based on studies with photodynamic therapy. Since the total lightload in photodynamic therapy is significantly higher and longer than during the measurements in this study, no SAEs and SUSARs are expected. Indeed, studies using the ALA plaster for mitoPO2 measurement in Rotterdam reported no serious adverse events and no SUSARs. These studies were performed on healthy volunteers, surgical patients and patients with chronic anaemia. However, these studies reported local side effects of the ALA plaster consisting of erythema, pruritus and transient hyperpigmentation. All these effects were temporary and disappeared mostly within 1-2 weeks' time. No local side effects or other adverse events were seen in our pilot study. To ensure the safety of our study participants, monitoring will take place during the study. Furthermore, the inclusion and exclusion criteria are optimised to minimize the risk for participants. Since safety is an important of our study, we will have attention for AEs, SAEs and SUSARs. With an independent expert on data safety monitoring board confirming the needlessness of a DSMB for the INOX ICU-2 study, no DSMB was initiated for this study either.

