### 9.2 Secondary study outcomes

Secondary study outcomes include:

- Description of between- and within-subject variability in healthy volunteers and neurosurgical patients in relation to the between- and within-subject variability of the INOX ICU-2 pilot study (P16.303)
- Report on adverse and serious adverse events of the mitoPO2 measurements.

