### *b. Previous exposure of human beings with the test product(s) and/or products with a similar biological mechanism*

Topical application of ALA is registered for use of photodynamic therapy of skin lesions. Its use for measuring mitoPO2 in healthy volunteers has been proven to be safe in the finished study with protocol number NL37911.078.11 in which the PpIX-TSLT technique was tested on 30 healthy volunteers. All healthy volunteers experienced the skin preparation and measurements as non-problematic. Due to either the skin preparation or the ALA patch, 45% of the volunteers suffered from mild pruritus and/or erythema on the actual measurement day; these minor complaints were no longer present the day after the measurements. Only two volunteers had transient hyperpigmentation of the skin after the measurements, possibly due to premature exposure of the primed area to sunlight (against our advice). The hyperpigmentation was temporary and disappeared within one month. None of the volunteers sustained long-term skin damage, as established one month after the experiments.

ALA was also used in finished study with protocol number NL56686.091.16 in May and June 2016 at UMC St. Radboud in Nijmegen. This study induced endotoxaemia in human volunteers. Among other measurements, the COMET measurement system and Alacare were used to measure oxygen availability and consumption. ALA was applied on the evening before the endotoxaemia day. The study again confirmed the safety profile of the COMET's measurement also during endotoxaemia. The measurements of the COMET identified change of mitochondrial function in vivo during human endotoxemia.

Other protocols use the same measuring technique: The running studies with Protocol nr: NL51187.078.14 (Photodynamic therapy study) and Protocol nr: NL51937.078.15 (Non-invasive monitoring of mitochondrial oxygen consumption and oxygenation (COMET): observational clinical study) and NL55664.078.15 (MOTIFATE pilot, a study of blood transfusion and fluid administration in chronic anaemia).

*c. Can the primary or secondary mechanism be induced in animals and/or in ex-vivo human cell material?*

Mitochondrial oxygen tension research has been performed in cells and animals prior to this research proposal. PpIX-TSLT is one of the central techniques used in translational research in the Laboratory of Experimental Anaesthesiology of Erasmus Medical Center.

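### Adverse event reporting is a declared outcome, but section 8.3 collects events passively: no skin assessment is scheduled at the readings and no contact after the last one, so local reactions have no denominator and late pigment change depends on chance report.

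*Protocol*

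**What the plan says.** Section 2.2 lists as objective 4, and section 9.2 repeats as a secondary outcome: "Report on adverse and serious adverse events of the" mitoPO2 measurements. Section 8.3 sets how events are found: "All adverse events reported spontaneously by the subject or observed by the investigator or his staff will be recorded".

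The last scheduled contact follows from section 7.2.1. T0 for patch 1 is "4 hours after ALA-induction (Directly after surgery in patient group) (=T0"), and patch 1 is last read 27 h later. The measurement log in section 5.1 names skin temperature, vasopressor use and dose, and nurse actions; it does not name skin reactions. Section 7.2 does not list them among the data collected either. Sections 5.1 and 5.2 require the site to be kept from sunlight for 24 h after the measurements.

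Section 8.7 follows every AE until it has abated or is stable. Section 11.5 ends the study on day 90 after the last ICU admittance, which is a study-level date and not a subject visit.

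On earlier experience, section 12 b reports a study in 30 volunteers. Pruritus and/or erythema occurred in 45% on the measurement day and was gone the day after. Two volunteers had hyperpigmentation, possibly from premature sunlight: "The hyperpigmentation was temporary and disappeared within one month". That study looked again later: "None of the volunteers sustained long-term skin damage, as established one month after the experiments". Section 8.8 says of local effects in earlier mitoPO2 studies: "All these effects were temporary and disappeared mostly within 1-2 weeks' time".

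**The concern.** A passive method counts what someone happens to mention or notice. For an outcome the protocol declares, this has three effects.

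- **Unreported symptoms.** Itch, burning and pain cannot be seen. An awake volunteer may mention them. A patient just out of surgery may be unable to, and section 4.1 allows for mechanical ventilation. The same procedure can therefore yield different counts in the two groups for reasons unrelated to the skin.
- **No record of absence.** An empty field can mean that the site was inspected and clear, that nobody looked, or that the subject could not answer. Without the number assessed, the report is a list of events and not a rate.
- **Late onset.** Hyperpigmentation from sunlight appears once the site meets daylight. After the last reading, nothing scheduled would detect it.

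At stake is the reading of a low count as evidence of safety. The variability endpoint is not affected.

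**Working it through.** **1. Last scheduled contact (section 7.2.1).** Induction is 4 h and patch 2 is applied 3 h after patch 1. In hours after patch 1:

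- Patch 1: 4 + (0, 1, 3, 6, 24, 27) = 4, 5, 7, 10, 28, 31.
- Patch 2: 3 + 4 + (0, 1, 3, 21, 24) = 7, 8, 10, 28, 31.

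The spans from T0 are 27 h and 24 h, which reproduces the 24-27 h per patch stated in that section. Both patches are last read at 31 h. In patients 31 h is a minimum, because induction lasts at least 4 h and T0 falls after surgery.

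**2. Sunlight window.** Protection is required for 24 h after the last reading, so to 31 + 24 = 55 h. From 31 h to 55 h the protocol relies on the precaution but schedules no observation of whether it worked.

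**3. Expected hyperpigmentation.** Input: 2 of 30 (sections 6.2 and 12 b). Assumption: this rate carries over.

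- Expected in 17 volunteers: 17 × 2/30 = 1.13.
- Chance of at least one: 1 − (28/30)^17 = 0.69.

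Two events make a weak estimate. The exact (Clopper-Pearson) 95% limits for 2/30 solve P(X ≥ 2 | 30, p) = 0.025 and P(X ≤ 2 | 30, p) = 0.025, giving 0.8% and 22.1%.

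| Rate assumed | Expected in 17 | P(at least one in 17) |
|---|---|---|
| 0.8% | 0.14 | 0.13 |
| 6.7% (2/30) | 1.13 | 0.69 |
| 22.1% | 3.75 | 0.99 |

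Applied to all 34 subjects, 2/30 would give 34 × 2/30 = 2.27 and 1 − (28/30)^34 = 0.90. Those figures also assume that postoperative inpatients meet sunlight as volunteers do, which nothing in the protocol supports, so I do not rely on them.

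**4. Why the denominator matters.** With zero events among n assessed subjects, the one-sided 95% upper bound is 1 − 0.05^(1/n). This is 16.2% for n = 17 and 8.4% for n = 34. Both hold only if every subject was assessed. Under section 8.3 the number assessed is not known, so neither bound can be claimed.

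**5. What the other figures show.** At 45%, pruritus or erythema would be expected in 17 × 0.45 = 7.65 volunteers. Section 12 b puts these on the measurement day, when the site is being handled, so this is not a number lost. The one to two weeks and the one month are durations. They do not say when a reaction begins, and a lesion present by 31 h can be seen at a reading however long it then lasts.

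**6. The pilot's safety record.** Sections 6.2 and 8.8 report no adverse reactions in the pilot, while section 12 e reports mild pruritus in one patient. The protocol does not say how the pilot collected events. These statements should be reconciled.

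**The case against.** The other side has good points.

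- **Erythema is in view.** At each reading the investigator uncovers the site, places the sensor and covers it again (section 5.1). Section 8.3 includes what staff observe. This stands for visible signs. It does not cover symptoms, and it leaves no record that a site was clear.
- **Contact is not shown to end at 31 h.** A reader might infer that it does. The protocol says only that nothing further is scheduled. Section 8.7 follows known events, a spontaneous report before the end of study can still be recorded, and patients may still be in hospital. This stands. The gap is in finding new or unreported reactions.
- **Reactions lasting weeks are not thereby missed.** A reader might compare 31 h of readings with one to two weeks or one month and conclude that most reactions escape. The documents do not support that, because the figures are durations, and section 12 b has the common reactions gone the next day.
- **The stopping rule does not depend on the patient speaking.** Section 12 j reads: "when there is any indication of a skin lesion (e.g. unexpected pain during the measurements), the measurements can and will be stopped". Pain is only the example, so no defect in that rule follows.
- **How many patients cannot report is unknown.** Section 4.1 expects a stable elective cohort. The 46% ventilated in section 8.4 is for Dutch ICU patients generally. This stands: the difference between groups is plausible but has no size.
- **Parts are not readable.** The measurement figure in section 5.1, the Appendix 2 diagrams, the consent pages and the eCRF are not in the text at hand. A skin check could appear there, which limits certainty about what is absent.
- **The outcome is only a descriptive report.** That is so, and comparison with the volunteer study is not an objective. Even a descriptive report needs to say how many subjects were assessed.

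**Conclusion.** The point holds in a limited form. Followed as written, section 8.3 gives a count of local reactions with no assessable denominator, leaves symptoms to whoever can and does report them, and leaves reactions that begin after about 31 h to chance report. An earlier study that the protocol relies on for safety did check skin at one month.

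The only part with a size is late hyperpigmentation: about 1.1 expected cases in 17 volunteers, with a range of 0.1 to 3.8 from sampling error in 2/30 alone. It rests on the volunteer rate carrying over to this study's patch use, light dose and sunlight behaviour. Section 12 i expects a lower light dose than in that study. For patients I give no figure. Nor can the number of unreported symptoms be estimated from the protocol.

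The change is worth making because the outcome is declared and the cost is small. It does not threaten the primary endpoint.

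**What to change.** In section 8.3 and the case report form:

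1. At each existing reading, record for each patch site whether a visible local reaction is present or absent. Where the subject can answer, record itch, burning and pain as present or absent; otherwise enter not assessable.
2. Add one short scripted contact per subject at about one month, by telephone or on the ward if still admitted, asking about pigment change, persisting lesions and sun exposure of the site.
3. Report local reactions per patch and per group, with the number assessable as denominator, and keep reactions seen at readings apart from those found at the later contact.

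If the eCRF or the Appendix 2 diagrams already hold a skin check, section 8.3 should refer to it, and only items 2 and 3 are new.

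Cost: a few fields at readings the research team already makes, and 34 short calls. The reported adverse event rate will probably be higher than under passive collection, and the report should say that the method is the reason. If only one item can be adopted, item 1 supplies the denominator at the readings; item 2 is what detects late pigment change.
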